   1. STUDY DESIGN

- The study is a monocentric prospective open labelled, randomized controlled superiority trial, with two parallel groups and balanced randomization stratified into 3 groups (according to patients prior diseases), with a 1:1 ratio, using random blocks of size 4, 6 and 8.
- Type of control : alternative strategy
- Level and method of blinding : none (open labelled study)
- Method of treatment assignment: randomization with stratification
- Number of subject : 94 patients (47 per group)
- Duration of study : 90 days

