In a pilot observational study on 88 patients, median time between first SBT and extubation was 22h with a strategy using SBT-PS and PEEP. We hypothesized that a between-arm difference of at least 24 hours would be clinically relevant to prefer a SBT strategy over one another. With an alpha risk of 5% and a bilateral hypothesis, a power of 80% and a hazard ratio of 2 (based on the ratio of median duration of time between first SBT and successful extubation), a total of 66 successful extubation would be needed. Accounting for both potential deaths before successful weaning and weaning failure (assumed to amount to 30%), we plan to include 94 patients (47 per group).

- 1. STUDY PROCEDURE

|  | Inclusion (day-1) | Day-2 to day-90 | ICU discharge / Death | Day-28 | Day-90 |
| --- | --- | --- | --- | --- | --- |
| Demographic data | X |  |  |  |  |
| Patient weaning readiness | X | X* |  |  |  |
| SBT result | X | X* |  |  |  |
| Arterial blood gas | X | X* |  |  |  |
| *If SBT success* |  |  |  |  |  |
| Cough score | X | X* |  |  |  |
| Abundancy of respiratory secretions | X | X* |  |  |  |
| Extubability criteria | X | X* |  |  |  |
| *If extubation* |  |  |  |  |  |
| Extubation date and time | X** | X** |  |  |  |
| Extubation type (protocolized/self-extubation) | X** | X** |  |  |  |
| Post-extubation NIV characteristics | X** | X** |  |  |  |
| Respiratory physiotherapy characteristics | X*** | X*** |  |  |  |
| High-flow nasal oxygen use | X | X*** |  |  |  |
| Invasive mechanical ventilation status | X | X*** |  |  |  |
| *If reintubation* |  |  |  |  |  |
| Reintubation criteria | X | X |  |  |  |
| *If tracheostomy performed* |  |  |  |  |  |
| Characteristics of tracheostomy |  |  | X |  |  |
| *Follow-up data* |  |  |  |  |  |
| Date/hour of cessation of invasive ventilation and NIV |  |  | X |  |  |
| End of study |  |  |  |  |  |
| Respiratory status |  |  | X | X | X |
| Mortality |  |  | X | X | X |
| *As long as the patient is intubated or tracheostomized  **On the day of extubation and the day after  ***during the 7 days following extubation  NIV denotes non-invasive ventilation, and SBT spontaneous breathing trial. | | | | | |

1. Population of Analysis (intention to treat population)

All subjects who were randomized except patients secondary excluded from the study due to:

- Transfer to another ICU not participating to the study
- Consent withdrawal
- Lack of inclusion criteria or presence of exclusion criteria

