   1. GENERAL METHODOLOGY

Quantitative variables will be will be described using the following statistics: number of missing data, mean, standard deviation, quartiles, minimum and maximum values, number and rate of missing variables, and compared between groups with the Mann-Whitney test. No normality check will be performed. Qualitative variables will be reported as absolute and relative frequencies, number and rate of missing variables, and compared between groups with the chi-2 test or the Fisher exact test. Variables will be compared between both groups, except for specific analysis described in 5.2. We will not adjust p-value for multiple comparison. Univariable absolute difference will be reported for each variable as difference [95% confidence interval]. The Hodges-Lehmann method will be used to compute unbiased median differences for outcomes and their CI95%. For qualitative variables, 95% confidence interval will be computed through bootstrapping.

P-value <0,05 with a bilateral hypothesis will be considered as significant. All the analyses will be carried out using R for Windows.

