5.2.5 Tertiary outcomes

Analysis will be carried out as described in 5.1.

Tracheostomy data will be reported a table with four columns (overall population, intervention group, control group, p-value) or in text if N<5.

We will report the following tertiary outcomes in a table with four columns (intervention group, control group, univariable absolute difference with 95% confidence interval, p-value):

- - Cause of end of protocol No reintubation in the 7 days following extubation; Withdrawing of care or withholding of reintubation decision; ICU discharge; death; patient still intubated at Day 90.
- Severe adverse event
- Respiratory status at ICU discharge (Day 28, Day 90)
- Successful extubation status
- Successful extubation rank
- Number of reintubation

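### Section 5.1 fixes bootstrap intervals for all differences in qualitative variables; with zero or very few events at 47 per arm they collapse or are too narrow (minor)

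*Protocol*

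**What the plan says.** Protocol section 5.1 (General methodology) asks for an absolute difference with a 95% confidence interval for each variable. For categorical data it names one interval method: "For qualitative variables, 95% confidence interval will be computed through bootstrapping". It does not say which bootstrap (percentile, basic, normal) or how many resamples, and it gives no other method for an arm with no events. The accompanying p-value comes from a different method, since categorical variables are "compared between groups with the chi-2 test or the Fisher exact test".

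The interval is then used in several tables:

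- Section 5.2.5 (Tertiary outcomes) gives "univariable absolute difference with 95% confidence interval, p-value" as columns for severe adverse events, cause of end of protocol (five categories) and respiratory status (seven categories in section 4.3), among others.
- Section 5.2.4 (Daily assessments) uses the same columns for reintubation criteria and aetiologies, in reintubated patients only.
- Section 5.2.1.2 uses them for the secondary outcomes.

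The one small-count rule, reporting in text when N is below 5, is in section 5.2.5. It covers only tracheostomy data, whose table has no interval column.

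**The concern.** The bootstrap estimates sampling variation by redrawing from the observed patients. An arm with no observed events can only be redrawn as an arm with no events, so it adds nothing to the estimated uncertainty. With 47 patients that is wrong: no events in 47 is compatible with a true rate of several per cent.

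At stake is how rare events are reported. If neither arm has a severe adverse event, the table would show a difference of 0 with interval [0, 0], which reads as certainty. If one arm has none, the interval is too short on the side where it matters. Because the p-value comes from an exact test, one row can also show an interval excluding zero beside a clearly non-significant p-value.

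**Working it through.** **Inputs.** 47 patients per arm (sections 2.1 and 2.5); two-sided 95% interval by bootstrap (5.1); chi-square or Fisher test (5.1). The protocol states no rate for any categorical outcome, so the true rates below are assumptions: 1% to 10% for rare and 15% to 30% for common. The percentile form of the bootstrap is also an assumption.

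**The plan's own figure.** The protocol gives no figure for these intervals; the relevant one is the sample size. For a hazard ratio of 2, two-sided 5% alpha and 80% power, the Schoenfeld formula gives 4 × (1.960 + 0.842)² / (ln 2)² = 4 × 7.85 / 0.480 = 65.4, hence 66, which agrees with "a total of 66 successful extubation would be needed". Then 66 / 0.70 = 94.3, or 94 patients and 47 per arm. This reproduces.

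**No events in either arm.** Every resampled difference is 0 - 0 = 0, so the percentile, basic and normal forms all give [0, 0], however many resamples are drawn. The Wilson upper limit for 0/47 is z²/(n + z²) = 3.84 / 50.84 = 7.6%, so the Newcombe interval for the difference is -7.6 to +7.6 points. The chance of this table is (1 - p)^94 when both arms share rate p:

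- 1%: 0.99^94 = 38.9%
- 2%: 15.0%
- 3%: 5.7%
- 5%: 0.8%

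**No events in one arm.** With x v 0 events, the lower percentile limit stays at 0 as long as a resample of the first arm has no event with probability above 2.5%, that is while (1 - x/47)^47 > 0.025. For x = 3 this is (44/47)^47 = 4.5%; for x = 4 it is (43/47)^47 = 1.5%. So at 1, 2 or 3 v 0 the limit is exactly 0, and at 4 v 0 it jumps to 1/47 = 2.1 points.

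| Events (47 per arm) | Percentile bootstrap, points | Newcombe, points | Fisher p |
|---|---|---|---|
| 0 v 0 | 0 to 0 | -7.6 to 7.6 | 1.0 |
| 1 v 0 | 0 to 6.4 | -5.6 to 11.1 | 1.0 |
| 2 v 0 | 0 to 10.6 | -3.9 to 14.2 | 0.49 |
| 4 v 0 | 2.1 to 17.0 | -0.6 to 19.9 | 0.117 |
| 5 v 0 | 2.1 to 19.1 | 1.0 to 22.6 | 0.056 |
| 14 v 9 | -6.4 to 27.7 | -6.8 to 27.3 | not computed |

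The Fisher value at 4 v 0 is 2 × C(47,4)/C(94,4) = 2 × 178,365 / 3,049,501 = 0.117. At 5 v 0 the score interval also excludes zero, so only the 4 v 0 row counts against the bootstrap in particular.

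**Coverage.** All 48 × 48 possible tables were enumerated with binomial weights, using the exact resampling distribution.

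| True rates | Percentile bootstrap | Newcombe |
|---|---|---|
| 1% v 3% | 72.8% | 99.8% |
| 1% v 5% | 89.1% | 98.7% |
| 2% v 5% | 89.5% | 99.0% |
| 5% v 10% | 91.6% | 97.0% |
| 15% v 30% | 94.2% | 95.2% |
| 1% v 1% | 99.8% | 100.0% |
| 5% v 5% | 95.9% | 98.1% |

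The first row can be checked by hand. If the 3% arm has no event (0.97^47 = 23.9%), the interval cannot reach the true difference of -2 points. If the 1% arm has none (0.99^47 = 62.4%) and the other has four or more (1 - 0.239 - 0.347 - 0.247 - 0.115 = 5.2%), it misses on the other side: 0.624 × 0.052 = 3.2%. Then 100 - 23.9 - 3.2 = 72.9%, against 72.8% by full enumeration.

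Mean width at 1% v 1% is 5.4 points, against 16.6 for the score interval. At 15% v 30% the widths match (32.6 v 32.7).

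**Other bootstrap forms.** The normal and basic forms cover 89.5% to 90.5% at 1% or 2% v 5%, and about 94% at 5% v 10%. At 4 v 0 the normal form also excludes zero: 8.5 ± 1.96 × √(0.0851 × 0.9149 / 47) = 8.5 ± 8.0, or 0.5 to 16.5. The basic form has its lower limit at 2 × 4/47 - 8/47 = 0.

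**Reintubated subset.** Assuming 10 patients per arm, percentile coverage is 64% at 5% v 10%. No events in either arm again gives [0, 0], against ±27.8 points for Newcombe.

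**The case against.** The strongest reply is that little depends on these intervals. Significance is judged by the p-value, which comes from a chi-square or exact test. Counts are printed beside the interval, so a reader of a 0 v 0 row sees how few events there were. The primary result is a Cox hazard ratio. The shortfall in coverage appears only when the true rates differ, and 73% is an extreme case with expected counts of 0.5 and 1.4 events (47 × 1% and 47 × 3%). The score interval is itself conservative at such rates. All of this stands, and it limits the point to a minor one. It does not rescue a rule that prints [0, 0] whenever neither arm has an event.

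Three stronger readings are tempting, and the protocol does not support them.

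- **False safety signals are inflated.** With equal true rates of 1%, 3%, 5% and 10%, the interval excludes zero in only 0.2%, 2.5%, 4.1% and 3.8% of trials.
- **Mortality and the other binary secondary outcomes are compromised.** Nothing shows that they will be sparse. Section 2.5 assumes that deaths before weaning and weaning failure together amount to 30%, about 14 of 47, without giving the split. At common rates the bootstrap performs adequately.
- **Coverage will be about 73% in this trial.** That needs specific rates and a specific bootstrap form, and the protocol states neither.

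It might also be said that this detail belongs in a statistical analysis plan. But the protocol does not leave it open; it names the method.

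**Conclusion.** The point holds, as a minor one. The collapse to [0, 0] when neither arm has an event needs no assumption about rates and is common to the percentile, basic and normal forms. The too-narrow interval with a zero in one arm, and its conflict with the Fisher p-value at 4 v 0, are also certain for the percentile form if such counts occur. The coverage figures are conditional on assumed rates.

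The rows exposed are those likely to be sparse: severe adverse events, categories of cause of end of protocol and of respiratory status, and reintubation criteria and aetiologies, where the denominator is below 47. That they will be sparse is itself an assumption. The primary analysis is unaffected and common binary secondary outcomes are little affected.

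**What to change.** In section 5.1, replace the bootstrap sentence by one stating that 95% confidence intervals for differences in proportions use the Newcombe or Miettinen-Nurminen score method. If the bootstrap is to be kept for common outcomes, the score method should at least apply wherever an arm has zero or few events, with the threshold stated in advance. The change applies equally to the reintubation table in section 5.2.4 and the tables in section 5.2.5.

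The cost is nil. Both methods are available in R, need no resampling or seed, and give practically the same interval as the bootstrap when events are common. A score interval will not agree with the Fisher test in every row, as 5 v 0 shows, so a short note that interval and p-value come from different methods would be useful.

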**HANDLING OF MISSING DATA**

Missing data are reported as NA and will not be imputed. Number of missing observations will be reported in tables. A summary of missing observations will be included in the supplementary material.

**SENSITIVITY ANALYSES**

A sensitivity analysis will be performed for the main outcome (cf. infra).

**SUBGROUP ANALYSIS**

An exploratory analysis will be performed on the following subgroups, on the primary judgment criterion.

- - - - Randomization strata
      - COVID status (COVID positive vs COVID negative)
      - Median bicarbonates on the day of extubation (lower than median vs. higher than median)
      - PaCO_2_ at the end of SBT ≥ 45 mmHg vs < 45 mm Hg, on the day of extubation
      - Time between intubation and inclusion below vs. greater or equal to its median value
      - Cough score below vs greater or equal to its median value

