  1. TREATMENT GROUPS

In this study, two strategies of weaning are compared: “assisted strategy” (intervention group) and “unassisted strategy” (control group).

Allocation sequence will be computer generated with stratification into 3 groups:

- Patients with chronic heart failure (CHF) (defined by an ejection fraction <45%)

- Patient with COPD or chronic respiratory failure

- Other patients

Randomization was done in each stratum with random blocks of size 4, 6 and 8.

Allocation sequence was concealed in a sealed opaque envelope with sequential number in each stratum. Allocation sequence was generated by a person independent from the investigator and not enrolling nor assigning patients to intervention.

Clinicians and investigators are enrolling patients and assigning patients to intervention according to the allocation.

Due to the type of intervention, no blinding is possible for the clinicians and the patients. During the database cleaning process, the statistician will be blind of the treatment allocation.

Patients are secondary excluded of the study if:

- Patient is transferred to another ICU
- Consent withdrawal
- Severe adverse event due to the study (on clinician decision)

These patients will be replaced.

- 1. STUDY POPULATION

Inclusion criteria:

• Patient 18 years old or more

• Intubated and ventilated in intensive care unit for more than 24 hours

• Patient ready for weaning evaluation

• Failure of a first SBT-TP

Exclusion criteria:

• Chronic neuromuscular disease

• Guillain-Barré Syndrome

• Central nervous system disease with consciousness disorder (i.e inability to obey a simple command)

• Tracheostomy

• Chronic disease with life expectancy less than 1 year

• Pregnancy, breast feeding

• Withholding life support regarding a reintubation

• Prisoner or patient interned in psychiatric hospital

• Under legal protective measures

• Language barrier

• Lack of social security

• Lack of the patient's consent (or of the next of kin where appropriate)

• Patient under an exclusion period after enrolment in another research study

- 1. INTERVENTION

The interventions will be started within the 6hr following inclusion.

Intervention group (assisted weaning strategy)

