- Chronic respiratory support: categorical variable (oxygen, NIV, both or none). Only for chronic respiratory failure patients.
- Chronic heart failure: categorical variable (yes or no)
- Charlson score: continuous variable, ranging from 0 to 43
- Baseline ventilator parameters:
  - Ventilation mode: categorical variable. Pressure support, volume controlled or other
  - Minute ventilation: continuous variable. Expressed in liters/min, with a precision of 0.1
  - Respiratory rate: continuous variable. Expressed in /min, as an integer
  - PEEP: continuous variable. Expressed in cmH2O, as an integer
  - FiO2: continuous variable. Expressed in %, as an integer
- Baseline arterial blood gas:
  - pH: continuous variable. Expressed without unit, with a precision of 0.01
  - PaCO2: continuous variable. Expressed in mmHg, as an integer
  - PaO2: continuous variable. Expressed in mmHg, as an integer
  - Bicarbonates: continuous variable. Expressed in mmol/L, as an integer
  - Base excess: continuous variable. Expressed in mmol/L, as an integer
  - Lactate: continuous variable. Expressed in mmol/L, as an integer

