**DAILY ASSESSMENTS**

These variables will be collected from Day 1 until Day 90:

- If the patient is intubated (SBT data):
  - Preliminary weaning criteria: categorical variable. Present or absent.
  - SBT result: categorical variable. Success or failure.
  - Arterial blood gas in case of SBT success:
    - pH: continuous variable. Expressed without unit, with a precision of 0.01
    - PaCO2: continuous variable. Expressed in mmHg, as an integer
    - PaO2: continuous variable. Expressed in mmHg, as an integer
    - FiO2: continuous variable. Expressed in %, as an integer. For control group, FiO2 is equal to 21+ 3*O2 flow on T-piece
  - Cough score: categorical variable. 0, 1, 2, 3, 4, 5
  - Abundance of respiratory secretions: categorical variable. 0, 1, 2, 3, 4
  - For intervention group: result of SBT-TP, categorical variable. Success or failure.
  - Summary of extubability criteria
    - Acceptable cough (cough score ≥3): categorical variable. Yes or No
    - Acceptable respiratory secretions (abundance of respiratory secretions ≤2): categorical variable. Yes or No
    - No general anaesthesia planned on the next 24h: categorical variable. Yes or No
    - No argument for laryngeal obstruction: categorical variable. Yes or No
    - Number of positive extubability criteria: numerical variable. Ranging from 0 to 4
  - Date (JJ/MM/AAAA)
  - Hour of extubation (HH:MM)
- If the patient is extubated (extubation data):
  - Patient extubated today: categorical variable. Yes or no
  - Extubation type: categorical variable. Programmed extubation per protocol; programmed extubation (protocol violation) or auto-extubation
  - Post-extubation prophylactic NIV (on the day of extubation and the following day): categorical variable. Yes or no
    - In case post-extubation prophylactic NIV:
      - Per-protocol: categorical variable. Yes or no
        - If per protocol, reason(s) for NIV

SBT-TP failure (for intervention group): categorical variable. Yes or no

Age>65 years old: categorical variable. Yes or no

COPD: categorical variable. Yes or no

Chronic heart failure: categorical variable. Yes or no

Chronic respiratory failure: categorical variable. Yes or no

PaCO2>45mmHg at the end of SBT: categorical variable. Yes or no

- - - - - Duration of NIV: continuous variable. Expressed in hours, as an integer
    - In case of no prophylactic NIV:
      - Reason: categorical variable. Per protocol, violation of protocol or contra-indication

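### Two exploratory subgroups of time to successful extubation are defined by values taken at extubation itself, and a third has no stated time point

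*Protocol*

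**What the plan says.** Section 5.1 (Subgroup analysis) names six exploratory subgroups for the primary outcome, time from inclusion to successful extubation. Three bear on this point:

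- bicarbonates: "Median bicarbonates on the day of extubation (lower than median vs. higher than median";
- arterial carbon dioxide, dichotomised on the value "at the end of SBT ≥ 45 mmHg vs < 45 mm Hg, on the day of extubation";
- "Cough score below vs greater or equal to its median value", with no time point.

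Other sections fix when these values exist:

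- Patients enter after "Failure of a first SBT-TP" (Section 2.3), and the assigned strategy starts within 6 hours of inclusion (Section 2.4).
- In Section 4.3 (Daily assessments) the daily gas is "Arterial blood gas in case of SBT success". It lists pH, PaCO2, PaO2 and FiO2, and no bicarbonates.
- Section 4.3 (Demography and baseline) has a "Baseline arterial blood gas" that includes both PaCO2 and bicarbonates. Cough score is not among the baseline variables.
- Section 5.1 (Handling of missing data) rules out imputation.
- Sections 4.1 and 5.2.1.1 censor patients without successful extubation at death or day 90.

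**The concern.** A treatment-effect subgroup should be fixed before the treatment can influence it. An extubation-day value fails that test twice when the outcome is time to extubation. It exists only for patients who reached extubation, and both who reaches it and in what state can depend on the arm. The patients who drop out are mainly those the primary Cox model keeps in the risk set as censored.

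PaCO2 raises a further problem. Section 2.4 has the SBT done with pressure support and PEEP in the intervention arm and on a T-piece in the control arm. One 45 mmHg cut applied to both need not pick out the same kind of patient in each arm.

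At stake is the forest plot promised in Section 5.2.1.1. Its rows for these subgroups would look like the primary effect within subgroups and would be something else.

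**Working it through.** **1. When each subgroup is known**

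| Subgroup (Section 5.1) | Time point stated | Can be fixed at inclusion? |
|---|---|---|
| Randomisation strata | at randomisation | yes |
| COVID status | none stated | yes |
| Time from intubation to inclusion | ends at inclusion | yes |
| Bicarbonates | extubation day | no, as written |
| End-of-SBT PaCO2 | extubation day | no, as written |
| Cough score | none stated | unclear |

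On cough score, two places differ. The schedule in Section 2.6 puts it under the condition "If SBT success". Since patients enter on a failed SBT, a score taken under that condition follows inclusion. Section 4.3 (Daily assessments) instead lists it for intubated patients at the same level as the SBT result, without that condition.

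**2. The plan's own figures** (Section 2.5: two-sided 5%, power 80%, hazard ratio 2, 30% without success)

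- Events: 4 × (z₀.₉₇₅ + z₀.₈₀)² / (ln 2)² = 65.35, rounded up to 66, as stated.
- Patients: 66 / 0.70 = 94.3, against the stated 94.
- Patients without successful extubation: 94 − 66 = 28 (0.30 × 94 = 28.2).

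**3. How many lack a value.** 28 is an upper limit. A patient extubated and then reintubated, or who died within 7 days of extubation, has an extubation day. The number never extubated is smaller, and the protocol does not give it.

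**4. What restriction can do to a hazard ratio of 2.** Both cases assume 30% non-events overall and drop all of them, which is more than the plan would drop.

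(a) *All non-events are deaths, at a constant hazard λ equal in both arms* (Section 5.2.1.1 itself assumes an identical competing risk). Set the extubation hazard to 1 in control and 2 in intervention.
- Success shares are 1/(1+λ) and 2/(2+λ). Their mean is 0.70 when λ = 0.592.
- Non-events are then 0.592/1.592 = 37.2% in control and 0.592/2.592 = 22.8% in intervention.
- Among patients with the event, times are exponential with rates 1+λ and 2+λ, so the hazard ratio is 2.592/1.592 = **1.63**.

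(b) *All non-events are patients still unweaned at the end.* If a share p is unweaned in control, proportional hazards gives p² in intervention.
- (p + p²)/2 = 0.30 gives p = 0.422 and p² = 0.178.
- Among patients with the event, when control survival has fallen to u, the hazard ratio is 2u/(u + p). It starts at 2/1.422 = 1.41 and falls to 1.00 at u = p.
- A Cox model on 400,000 simulated patients gives **1.25**, against 2.00 with everyone kept.

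**5. What else is unsettled in the definitions**

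- Bicarbonates are not listed in the daily gas. They might be calculated from pH and PaCO2, but the protocol does not say so.
- The intervention arm can have two SBTs on one day, and Section 5.1 does not say which one supplies PaCO2. Section 4.3 gives a T-piece FiO2 formula for the control group only, which suggests that the intervention-arm gas is taken under assistance.
- After a reintubation, Section 5.1 does not say which extubation counts.

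**The case against.** The strongest reply is about weight. The subgroups are labelled exploratory. The sample size, the primary Cox model and the Fine and Gray sensitivity analysis do not depend on them, and missing counts will be reported, so the loss of patients would be visible. All of that stands and limits the severity. It does not remove the problem: the exploratory label tempers the strength of inference but does not correct selection on the outcome.

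Three stronger readings are tempting, and the documents do not support them.

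- *That three subgroups are plainly post-randomisation and undefined for the never-extubated.* This is explicit for two. Cough score has no time point in Section 5.1, and Sections 2.6 and 4.3 differ on its collection. A patient who passes an SBT without being extubated can also have a score.
- *That the hazard ratio would fall to 1.25 with 28 patients lost.* That figure needs every non-event to be a patient still unweaned, whereas Section 2.5's 30% covers deaths as well. The count of 28 is only a ceiling.
- *That measuring PaCO2 under different support would create a spurious interaction.* The protocol gives no size for any such shift. Suppose PaCO2 reads 3 mmHg lower under pressure support, has mean 43 and SD 7, and the extubation hazard falls 5% per mmHg, with no treatment effect. The hazard ratios are then about 0.88 to 0.92 above the cut and 0.92 to 0.93 below it, depending on censoring. That is a small shift in both subgroups. With 66 events split 31%/69%, the standard errors of the log hazard ratios are √(4/20.5) = 0.44 and √(4/45.5) = 0.30, far larger than any difference between the two.

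It is also fair to say that a baseline gas answers a somewhat different question from PaCO2 during the SBT.

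**Conclusion.** The point holds for two of the six subgroups. Bicarbonates and end-of-SBT PaCO2, as defined, are post-randomisation values taken in effect at the outcome. They are undefined for patients never extubated, and for PaCO2 the measurement conditions differ by arm. Cough score is probably in the same position as scheduled, but its timing is first of all unspecified.

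The size depends on assumptions. At most about 28 of 94 patients would lack a value. Restriction to patients with the event would move a true hazard ratio of 2 to between about 1.25 and 1.63. The range rests on the plan's 30%, on proportional hazards, and on dropping every non-event, so it shows the mechanism and does not predict the result. The conclusion is that these subgroup hazard ratios would not estimate the primary effect within subgroups. It does not extend to the primary analysis or to a demonstrable false interaction. The change should be made, but the trial does not turn on it.

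**What to change.** - Define the bicarbonate and PaCO2 subgroups on the baseline arterial blood gas in Section 4.3, after confirming that it is drawn before randomisation, which the protocol does not state.
- Analyse them with the strata-adjusted Cox model of Section 5.2.1.1 on the analysis population of Section 3.
- Reconcile Sections 2.6 and 4.3 on when cough score is collected. Use it as a subgroup only if a pre-randomisation value exists; otherwise drop it as a treatment-effect subgroup.
- Keep extubation-day values as descriptive data only, as Section 5.2.4 already plans for successfully extubated patients.

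The cost is small and needs no new data collection. Baseline PaCO2 is not PaCO2 during the SBT, so that subgroup's question changes somewhat, and one exploratory subgroup may be lost.
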